
**Fig. 2 Fig2:**
[figure not shown]
Perioperative protocol of anesthesia

### Intervention

Patients in TEAS group will be treated bilaterally at four acupoints: Hegu (L14), Neiguan (PC6), Zusanli (ST36) and Shangjuxu (ST37). L14 is the primary acupoint of the hand yangming large intestine meridian, which is located on the dorsum of both hands between the first and second metacarpal bones (Fig. 3A). PC6 belongs to the pericardium meridian, located on the palmar side of the forearm, 2 cun above the rasceta, between the palmaris longus tendon palmar tendon and the flexor carpi radialis muscle tendon (Fig. 3A). ST36 and ST37 are acupoints of the Yangming stomach meridian. ST36 is situated at the lateral side of the lower leg, on the line of Dubi and Jiexi, 3 cun below Dubi and one finger width lateral to the anterior border of the tibia (Fig. 3B). ST37 is located 3 cun below ST36. The “cun” in traditional Chinese medicine generally refers to “the same body size”. The distance between the radial ends of the first and second transverse patterns of the patient’s middle finger is “1 inch”. Four fingers, excluding the thumb, are placed side by side and generally refer to “3 cun”. Self-adhesive electrodes with wires will be attached to the locations of these acupoints and will be connected to the HANS acupoint nerve stimulator (HANS-200A, Nanjing Jisheng Medical Technology Co., Ltd., China). The current frequency will be set at 2 and 100 Hz. A dense-dispersed wave will be applied, alternating the frequencies every 3 s. The stimulation intensity will be set at the level of maximum tolerance for patients. The TEAS stimulation will start at 30 min before the surgery until the end of the operation.

**Fig. 3 Fig3:**
[figure not shown]
The location of acupoint. **A** The location of L14, PC6. *L14 is Hegu acupoint; PC6 is Neiguan acupoint*. **B** The location of ST36, ST37. *ST36 is Zusanli acupoint; ST37 is Shangjvxu acupoint*. This figure was drawn by the corresponding author of this manuscript [name] [14]. Permission was obtained

In the control group, two of the sham points are at 7 cun above and 1 cun outside Shenmen (HT7), and 9 cun above and 1 cun outside HT7 (Fig. 4A). The other two sham points are located at 9 cun and 12 cun above the Kunlun (BL60) (Fig. 4B). Self-adhesive electrodes with wires will be also sticked to the sites of these acupoints and will be connected to the HANS acupoint nerve stimulator. However, no power will be supplied to the stimulator. Analog pulses will be used at the same time 30 min before the surgery until the end of the operation (Fig. 5).

**Fig. 4 Fig4:**
[figure not shown]
The location of sham point. **A** The location of sham point 1 and 2. *HT7 is Shenmen acupoint*. **B** The location of sham point 3 and 4. *BL60 is Kunlun acupoint*. This figure was drawn by the corresponding author of this manuscript [name] [14]. Permission was obtained

**Fig. 5 Fig5:**
[figure not shown]
The administration of TEAS treatment protocol

### Outcomes

#### Primary outcome

The primary outcome is post-operative pain (VAS) score at the time of entering PACU, 10 min, 20 min, 30 min, 1 h, 2 h, 4 h, 6 h, 18 h, 24 h, 48 h after the surgery. The incidence of post-ESD VAS ≥ 4 and the consumption of morphine during follow-up will also be recorded.

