### Sample size calculation

The primary outcome of this study is the postoperative VAS score. In accordance with the pre-experimental results, there will be no severe postoperative pain until 1 h after the surgery. Therefore, sample size was calculated based on the VAS score at 1 h after the ESD procedure. The mean VAS at 1 h in TEAS group and the sham group in the pre-experiment was 0.86 ± 1.14 and 1.68 ± 1.46, respectively. The PASS 11.0 software was used, with unilateral α = 0.05, β = 0.1 and power = 0.90. A total of 55 effective samples were estimated for each group. Considering of 10% patient loss, we set 60 cases for each group in this study. Eventually, we will involve 120 cases, including 60 patients in the TEAS group and 60 patients in the control group (30 in esophageal ESD and 30 in gastric ESD procedure). Our digestive endoscopy center performs 300–400 upper gastrointestinal ESD surgeries, so this trail period is set at 16 months consequently.

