### Statistical analysis

Statisticians will negotiate with the research team to establish statistical analysis plans, develop databases, and perform statistics with the SPSS statistical analysis system. Statistics analyses include demographic and other baseline characteristics, postoperative pain degree analysis, statistical analysis of recovery time of gastrointestinal function, the incidence of complications and combined treatments, and comprehensive efficacy evaluation. Statisticians will use mean ± standard deviation (SD) to express measurement data that meet the normality test and use t-test to analyze. Non-parametric measurement data will be described as median and interquartile range (IQR), and Wilcoxon signed rank test will be applied. Enumeration data will be expressed as numbers and percentages. Pearson’s chi-squared test and Fisher’s exact test will be the methods applied for these data. Univariate logistic regression analysis will be applied to analyze risk factors which are reported to have possible correlation with VAS ≥ 4 in previous studies. Variables which are considered statistically significant (*P* < 0.05) will be selected for multivariable logistic regression to explore the association of those with post-ESD VAS ≥ 4. The Hosmer-Lemeshow test will be used to evaluate goodness-of-fit of the model. All *P* values above are unilateral and *P* < 0.05 will be considered significant. Subgroup analysis will be conducted in accordance with different procedure types. Intention to treat (ITT) principle will be applied to analyze all data. Because all the data will be collected during hospital stay by a conscientious observer (except for the last entry of QLQ-C30 life quality scale, which will be completed at a month after surgery), missing data can be mostly avoided. The mean imputation method will be used if missing data still preserves. The Capital Medical University statistical department will determine detailed analyzing methods for the main efficacy indicators.

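### The primary outcome is VAS at eleven times with no primary time point or success rule, while the sample size and 90% power rest on VAS at 1 h only

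*Protocol article*

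**What the plan says.** The Primary outcome section of the protocol article states: "The primary outcome is post-operative pain (VAS) score at the time of entering PACU". The list continues with 10, 20 and 30 min and 1, 2, 4, 6, 18, 24 and 48 h, which makes eleven assessments with PACU entry counted as the first. The Abstract gives the same list. Neither place singles out one time, defines a summary (mean, peak or area under the curve), or says what pattern of results would count as a positive trial. The incidence of VAS ≥ 4 and morphine consumption are to be recorded as well. They appear under the primary heading and are absent from the secondary list.

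The Sample size calculation section begins with "The primary outcome of this study is the postoperative VAS score", again without a time. It then says that the pre-experiment showed no severe pain until 1 h after surgery, and that for this reason the "sample size was calculated based on the VAS score at 1 h after the ESD procedure". The pilot VAS at 1 h in the TEAS and sham groups "in the pre-experiment was 0.86 ± 1.14 and 1.68 ± 1.46", and the calculation was run "with unilateral α = 0.05, β = 0.1 and power = 0.90". The result is 55 per group, raised to 60 for losses.

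The Statistical analysis section gives a t-test or a Wilcoxon test for measurement data. It says that all P "values above are unilateral and" that P < 0.05 is significant. It leaves detailed methods for the main efficacy indicators to the university's statistics department.

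**The concern.** A trial needs one defined comparison on which success is judged, or a stated rule for combining several. Here the outcome section offers eleven scores on equal footing and the sample size section uses one of them, without saying that this one is the primary time point. Two things follow.

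First, the 90% power belongs to a comparison that the outcome section does not set apart from the other ten. Second, a difference at any one of the eleven times could later be presented as a positive primary result, because nothing in the text rules that out.

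The matter is pressing because the Trial status section reports 70 participants already included. The Data collection methods and monitoring section also has the Data Monitoring Committee unblind and weigh effectiveness midway, and the text gives it no single primary comparison to weigh.

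**Working it through.** **1. Does the stated sample size correspond to one time point?**

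Inputs from the Sample size calculation section: means 0.86 and 1.68, SDs 1.14 and 1.46, power 0.90, alpha 0.05.

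- Difference: 1.68 − 0.86 = 0.82.
- Pooled variance: (1.14² + 1.46²)/2 = (1.2996 + 2.1316)/2 = 1.7156, so SD = 1.310.
- Per-group n (normal approximation): 2 × SD² × (z for alpha + z for power)² / difference², where 2 × 1.7156 / 0.82² = 5.103.
- One-sided 0.05: 5.103 × (1.645 + 1.282)² = 43.7, so 44 (45 with the t distribution).
- Two-sided 0.05: 5.103 × (1.960 + 1.282)² = 53.6, so 54 (55 with the t distribution).
- One-sided 0.05 with the larger SD of 1.46 in both groups: 2 × 2.1316 / 0.6724 × 8.564 = 54.3, so 55.

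The stated 55 is therefore reproduced as a single 1 h comparison, either two-sided with both SDs or one-sided with the larger SD. Under either reading there is no allowance for further time points. That 55 does not follow from the stated one-sided alpha with both SDs is a separate matter.

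**2. What if any one significant time counted as success?**

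If the eleven tests were independent, the chance of at least one false positive would be 1 − 0.95¹¹ = 0.431. Repeated scores in the same patient are correlated, so this is an upper figure. The documents give no correlation, so a range is assumed. Eleven correlated one-sided z tests were simulated with no true effect (400,000 draws):

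| Assumed correlation | Same correlation between all times | Serial correlation (AR(1)) |
|---|---|---|
| 0.5 | 25.9% | 35.3% |
| 0.7 | 19.2% | 28.6% |
| 0.8 | 15.7% | 23.8% |
| 0.9 | 11.8% | 17.7% |

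Against a nominal 5%, this is about 2 to 7 times too high (11.8/5 = 2.4; 35.3/5 = 7.1).

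**3. What if all eleven had to be significant?**

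The same simulation with equal correlation gives a false-positive chance of about 0.03% at 0.5 and 1.3% at 0.9, so there is no inflation. Power then cannot exceed the power at the weakest of the eleven times. It cannot be computed, because the documents give an effect size for 1 h only.

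**4. What would each way out need?**

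- One test at 1 h: 55 per group gives 94.7% power at one-sided 0.05, or 90.2% at two-sided 0.05 (t-test). No increase is needed.
- All eleven kept with a Bonferroni split: alpha = 0.05/11 = 0.00455, z = 2.609. Then n = 5.103 × (2.609 + 1.282)² = 77.2, so 78 per group for 90% power at the 1 h effect, and 78/0.9 = 86.7, so 87 after 10% loss. With 55 per group, power at 1 h would be 75.0%; with 60 it would be 79.4%.

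**The case against.** The protocol does not say that eleven separate VAS tests will be run. The outcome section lists when VAS is scored, and the Statistical analysis section gives tests by type of data. That section also says that an analysis plan will be drawn up and that the statistics department will decide detailed methods for the main efficacy indicators. The handling of multiplicity and the model for the time course are commonly left to such a plan, so their absence here is not a fault. The sample size section even gives a reason for choosing 1 h, and a reader can guess that 1 h is the key time.

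Most of this stands. A reader might infer that each time will be tested at 0.05 and that false positives will therefore multiply. The text does not support that as a fact: it depends on an any-one-suffices rule that appears nowhere, and an all-must-succeed rule would have the opposite effect on error. A reader might also infer that the four assessments before 1 h are expected to show little pain. The document says only that there was no severe pain by then. Nor do VAS ≥ 4 and morphine consumption add two more primary tests, since they are only to be recorded, though their place in the outcome hierarchy is unclear.

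What the objection does not answer is the mismatch within the protocol. Which time point is primary is part of the outcome definition, and deferring detailed methods does not cover it. The sample size section itself calls the primary outcome the postoperative VAS score with no time attached, so the choice of 1 h is a basis for sizing and not a designation.

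**Conclusion.** The point holds as a mismatch between the outcome defined (VAS at eleven times) and the outcome powered (VAS at 1 h), with no primary time, summary measure or success rule to join them. The defect is that the rule is undefined.

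Its effect depends on how the gap is later filled. Under an any-one-suffices reading, the chance of a false result in favour of TEAS is about 12% to 35%. This rests on correlations of 0.5 to 0.9, which are assumed and not taken from the documents. Under an all-must-succeed reading, error is controlled but the 90% power does not describe the trial. Since either reading is open, the protocol needs correcting, and before anyone sees unblinded results.

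**What to change.** In the Abstract, the Primary outcome section and the Sample size calculation section, state that the single primary outcome is the VAS score at 1 h after ESD, compared between groups once at the stated alpha. List the other ten time points, the incidence of VAS ≥ 4 and morphine consumption under Secondary outcomes. The model for the time course can be left to the statistical analysis plan.

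A prespecified summary score or one longitudinal test would also give a single primary test. Naming 1 h is the simplest route because it is the sponsor's own basis for sizing and keeps the planned 120 patients. The cost is a wording amendment. The small downside is that effects at other times become supportive only.

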### Data collection methods and monitoring

The observer, under the instruction of statistical professionals, gathers data including the basic information of patients enrolled, primary and second outcomes, incidence of complications, AEs etc. All the original data needed will be recorded accurately and completely in the case report forms (CRF). Any defective cases will be recorded, for example, in which patients forget their time to first flatus, first defecation, first liquid drinking and tolerance of a solid diet. All the period of this study will be monitored by Data Monitoring Committee (DMC), which consists of a doctor responsible for data collection and sorting, a statistician and a scientific research manager. DMC will be independent from the sponsor and competing interests. They will perform unblinding and weigh effectiveness and safety in the middle stage of this clinical study, and make the decision of continuing the trail, adjusting the protocol, or terminating the test, with communication to IRBs. At the end of the research, the distribution information, the original data and results will be presented to the scientific research management committee, who have access to the final trial dataset; they will be kept unknown to the public before the results are published.

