### Randomization and blinding

This is a single-blinded study. To minimize evaluation bias, the evaluators responsible for screening and outcome evaluation will be blinded to the grouping information. The anesthesiologist, and the acupuncturist who is in charge of the TEAS stimulation from the traditional Chinese department, will acknowledge each patient’s affiliation, but will be isolated to the research results. Patients will not be informed about their group assignment. Randomization will be performed by a computer-generated blocked randomization order. A nurse will generate the allocation sequence and prepare the sealed, numbered envelops. Each envelop will be unfolded by the anesthesiologist until the patient entering the operating room. Subjects will be randomly assigned to the sham group or the TEAS group with a ratio of 1:1 by the anesthesiologist according to these envelops. The case report forms (CRF) will be used to record all the original data needed.

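### The DMC's unblinded mid-trial effectiveness review leaves type I error unprotected as written, and its membership conflicts on its face with the blinding of outcome evaluators

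*Protocol article*

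**What the plan says.** The section Data collection methods and monitoring gives the DMC an active role: "They will perform unblinding and weigh effectiveness and safety in the middle stage of this clinical study". After that review it decides, in communication with the IRBs, whether the trial goes on, is adjusted or is ended. No number of looks, exact timing, stopping boundary or limit on permitted changes is given.

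The same section describes the committee as one "which consists of a doctor responsible for data collection and sorting, a statistician and a scientific research manager". It states independence from the sponsor and from competing interests. It separately names an observer who gathers the primary and secondary outcomes.

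The section Randomization and blinding promises that "the evaluators responsible for screening and outcome evaluation will be blinded to the grouping information".

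The section Sample size calculation is for a single final comparison, "with unilateral α = 0.05, β = 0.1 and power = 0.90". The section Statistical analysis says that all P "values above are unilateral and" sets significance at P < 0.05.

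**The concern.** There are two separate problems.

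The first is error control. An unblinded comparison of effectiveness that can end the trial is an extra opportunity to declare benefit. If the final test still uses the whole 0.05, nothing is set aside for that opportunity. Changing the protocol after seeing effectiveness by arm opens a further route to bias, which a final threshold alone does not correct.

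The second is blinding. The committee that unblinds includes a person responsible for data collection while data are still being collected. The primary outcome is a subjective VAS score at 11 time points. The active arm is stimulated at maximum tolerance and the sham stimulator is unpowered, so patient blinding may be fragile and evaluator blinding carries much of the protection. If the DMC doctor also gathered outcomes after the review, that protection would be weakened, and no analysis could restore it.

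**Working it through.** **1. The plan's own sample size.** Inputs from Sample size calculation: mean VAS at 1 h in the TEAS and sham groups "was 0.86 ± 1.14 and 1.68 ± 1.46, respectively"; one-sided alpha 0.05; power 0.90. The result given is: "A total of 55 effective samples were estimated for each group".

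- Difference = 1.68 − 0.86 = 0.82. Pooled SD = √((1.14² + 1.46²)/2) = 1.310.
- Formula: n per arm = 2·SD²·(z for alpha + z for power)²/difference².
- One-sided, SD 1.46 in both arms: 2 × 1.46² × (1.645 + 1.282)²/0.82² = 54.3, so 55.
- Two-sided 0.05, pooled SD: 2 × 1.310² × (1.960 + 1.282)²/0.82² = 53.6, so 54 (55 with the t distribution).
- One-sided, pooled SD: 43.7, so 44 (45 with the t distribution), which does not match.

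The figure of 55 is thus reachable by two standard routes. Which one was used is a side question. What matters here is that each is a fixed design with one final test, with no allowance for an interim look.

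**2. Error rate with one interim efficacy test.** Assumptions, none of them in the document: one look, benefit tested on the 1 h VAS comparison, stopping on success. The information fraction f is taken as 0.50 for a mid-trial look, with 0.33 to 0.67 as the range. Under the null, the interim and final z statistics are bivariate normal with correlation √f, and

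overall error = 1 − P(Z₁ < c₁ and Z₂ < c₂).

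| Interim one-sided level | Final one-sided level | f | Overall one-sided error |
|---|---|---|---|
| 0.05 | 0.05 | 0.33 | 0.085 |
| 0.05 | 0.05 | 0.50 | 0.080 |
| 0.05 | 0.05 | 0.67 | 0.074 |
| 0.001 | 0.05 | 0.50 | 0.0502 |
| 0.0005 | 0.05 | 0.50 | 0.0501 |

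Check at f = 0.50 with c₁ = c₂ = 1.645: P(neither test rejects) = 0.920, so the error is 1 − 0.920 = 0.080. With no efficacy stopping and the design otherwise unchanged, the error stays at 0.05 or below.

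**3. Boundaries that hold exactly 0.05 at f = 0.50, one-sided.** O'Brien-Fleming: 0.0088 at the interim and 0.0467 at the end. Pocock: 0.0304 at each look. Haybittle-Peto with interim 0.001: 0.0498 at the end.

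**4. Blinding, section against section.** Randomization and blinding keeps outcome evaluators blind. Data collection methods and monitoring gives the unblinding to a committee that includes a doctor in charge of collecting data. It assigns outcome gathering to an observer and does not say whether the two are one person. If they are, the sections contradict each other; if not, they can be reconciled in a sentence.

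**5. Timing.** Trial status reports 70 participants included of 120 planned: 70/120 = 58%, leaving 50 to enrol. A halfway review would already be due or past.

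**The case against.** The strongest reply on error rate is that the article contains no interim hypothesis test, no interim P threshold and no rule to stop for benefit. Weighing effectiveness could mean futility only, and stopping only for harm or futility does not inflate type I error. Boundaries also commonly sit in a SAP or DMC charter, and the article says analysis plans will be drawn up. This stands to the extent that 8.0% cannot be given as the trial's error rate. It does not remove the point. The article itself states an unblinded effectiveness review with power to terminate or adjust, next to an unreduced final threshold, and nothing in it confines that power to harm or futility.

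On blinding, a reader might infer that outcome collection is already compromised for every patient after the review, up to 60 of 120. The documents do not support that. The DMC doctor is not identified as the observer. A mid-trial unblinding shows the groups of patients already enrolled, and nearly all of these would have passed the 48 h end of VAS follow-up. Later allocations stay in sealed envelopes until the patient enters the operating room. VAS is the patient's own rating and bowel recovery times come from a self-completed form, which limits what a collector could influence.

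A reader might also see the DMC's claim of independence as contradicted. It is not: the claim covers the sponsor and competing interests, not the conduct of the trial. Wider independence is a fair recommendation, but its absence is not an inconsistency.

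**Conclusion.** The point holds in a limited form. As written, the plan permits an effectiveness-driven decision mid-trial and still spends the full one-sided 0.05 at the end, so type I error is unprotected. The size depends on a rule the article does not give. It runs from about 5.0% with a strict interim bar to 8.0% if benefit is tested once at one-sided 0.05 at half the information with stopping on success (7.4% to 8.5% for fractions 0.67 to 0.33). The upper figure is a worst case for a single look, not an estimate of what the trial will do. Protocol adjustment on unblinded effectiveness is an additional exposure, not included in those figures.

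The DMC membership and the evaluator blinding conflict on their face and must be reconciled. A breach is possible but not shown. It would be too strong to say that either error control or blinding has failed.

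**What to change.** - **Purpose of the look.** Preferably limit the mid-trial review to safety. If effectiveness stays, state the number and timing of looks and a Haybittle-Peto rule on the plan's own one-sided scale: for example, stop for benefit only if one-sided P < 0.0005 and keep the final test at one-sided 0.05 (total about 0.0501 at half the information).
- **Adaptations.** State that unblinded effectiveness data will not drive protocol changes.
- **Access.** Give unblinded tables only to the statistician and to members with no role in collecting outcomes. Keep the data-collecting doctor in blinded sessions, and say whether this person is the observer.
- **Record.** As 70 of 120 patients were already included, document whether the look has taken place, what was reviewed and who saw allocations. If it has, adopt these rules openly as a later amendment and report them as such.

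The cost is a few sentences and a short file note, with no extra staff. The downside is less freedom to stop early for benefit.
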